## Abstract

**Background/Objectives**: Radiation therapy is a common treatment modality for non-small-cell and small-cell lung cancer that can be associated with considerable side effects, mainly reactions of healthy tissues in the radiation field. Radiation therapy may lead to significant fatigue, which can potentially be mitigated by maintaining or increasing physical activity during treatment. Since achieving this goal may be a challenge for patients, they may benefit from a mobile application reminding them daily to perform a predefined number of steps. Such a reminder app will be investigated prospectively in a phase 2 trial. The current APART-LUNG study (NCT07380815) is a mandatory study for designing the prospective trial. **Methods**: The main objective of the APART-LUNG (exploratory non-interventional) study is to report patterns of physical activity during radiation therapy for lung cancer patients and generate hypotheses based on our findings. Our primary endpoint is the within-patient difference in weekly average steps per wear hour of the smartphone (week 5 minus week 1 of radiation therapy), and our secondary aim is to estimate differences in operational measures (wear time of the smartphone) between week 5 and week 1. The sample size of approximately 20 patients (full analysis set) allows us to detect a moderate-to-large standardized within-patient difference and is driven by feasibility and the intent to obtain preliminary estimates of effect size and variability. The results of the APART-LUNG study will be very important for appropriately designing a phase 2 trial.

## 1. Introduction

A considerable number of patients with lung cancer receive radiation therapy [1,2], an anticancer treatment that can lead to considerable side effects, including fatigue, which may result in a reduced intensity of physical activity [3,4,5,6,7,8,9]. Patients who experience significant fatigue may be unable to complete their entire radiation therapy course as initially planned.

The importance of exercise and physical activity for lung cancer patients has been highlighted in several review articles [10,11,12,13,14]. In a study including cancer patients, of whom 31 were treated with chemotherapy for lung cancer, exercise was shown to lead to fewer dose reductions and treatment delays [15]. Furthermore, patients’ quality of life may be improved if they are physically active [16,17,18,19,20,21,22]. In one retrospective study of lung cancer patients treated with chemotherapy, a relationship between physical activity and time to death was observed [23], supporting the importance of physical activity during anticancer treatments such as radiation therapy. Adherence to regular exercise can be a challenge for patients, particularly if side effects occur [24,25]. The best option to increase physical activity will likely be in-person kinesiology activities, such as in-person group exercise programs, physical therapy, or yoga programs. Videos, online courses, and mobile applications (reminder apps) may be less effective but could potentially be helpful. As part of the Interreg project Health Advancing Technologies for Elderly (HeAT), an app for patients’ smartphones that reminds them several times a day to walk a predefined number of steps has been created. The potential effect of this reminder app on a patient’s physical activity will be tested in a phase 2 trial. However, the step counts derived from smartphones are influenced by variability in device carrying time, and this variability introduces measurement heterogeneity that must be explicitly addressed in the statistical design and analysis. This study is a pilot investigation for a phase 2 trial evaluating changes in physical activity during radiation therapy and is a prerequisite for designing the phase 2 trial. The APART-LUNG study was approved by the German ethics committees of the University of Lübeck and the Christian Albrechts University, Kiel.

## 2. Study Design and Materials

### 2.1. Objectives and Endpoints

The primary objective of the APART-LUNG study is to estimate the within-patient changes in physical activity between week 1 and week 5 of radiation therapy, measured using smartphone-recorded step counts normalized for the device-carrying time. Week 5 of radiation therapy was chosen because we would like to receive information about the patients’ physical activity during the treatment course and since most patients treated with conventional fractionation receive at least 50 Gy administered over five weeks (five fractions of 2.0 Gy per week). To account for inter- and intra-individual variability in device usage, normalized daily step counts are calculated as the total daily steps divided by the estimated daily smartphone carrying time expressed in hours. Our main question relates to the course of the mean number of steps during the weeks of radiation therapy, namely, whether it will remain almost constant or become lower. The latter option appears more likely (hypothesis). Our secondary objectives are to examine operational measures such as wear times, to assess the feasibility of the primary endpoint, and to explore heterogeneity in the primary endpoint across relevant subgroups (considering the rather limited sample size of this study).

The APART-LUNG study is a pre-study for a prospective phase 2 trial that will investigate the value of a reminder app. This study is necessary for the optimal creation of the study protocol and calculation of the required number of study participants, and the cohort of the present study will serve as a control group for the phase 2 cohort using the new reminder app.

Our secondary objective is to estimate the differences in operational measures (wear time of the smartphone) between week 5 and week 1. In addition, the feasibility of the primary endpoint will be assessed, including the proportion of patients with both weeks evaluable and operational reasons for non-evaluable pairs. Moreover, the heterogeneity of week 5 and week 1 changes across subgroups, namely, age categories (<65 vs. ≥65 years), pre-treatment performance status, and histology (NSCLC vs. SCLC), will be explored.

### 2.3. Eligibility Criteria

Inclusion and exclusion criteria for the APART-LUNG study are given in Table 1.

### 2.4. Sample Size Calculation

The study is designed as a pilot and feasibility investigation and is not intended to provide confirmatory evidence. The sample size of approximately 20 patients is driven by feasibility and the intent to obtain preliminary estimates of effect size and variability, and formal hypothesis testing power is not targeted. Nevertheless, an illustrative sample size justification based on standardized differences is provided to support the planned enrollment of approximately 20 patients: the standardized effect size for the primary endpoint is defined as Cohen’s d for paired data, calculated as the mean within-patient difference in weekly normalized step counts divided by the standard deviation of these differences. With a sample size of 20 patients, a two-sided significance level of 5%, and 80% power, the study is capable of detecting standardized within-patient differences of approximately 0.6 to 0.65, corresponding to moderate-to-large effects. This level of sensitivity is considered appropriate for the exploratory objectives of the study. The sample size allows for a reasonably precise estimation of effect sizes and variability while remaining feasible in the context of a pilot investigation. All inferential results will be interpreted descriptively and will primarily serve to inform the design of future confirmatory trials.

## 3. Detailed Procedure

### 3.1. Overview of Examinations and Data Assessed at Baseline

An assessment of the data required for the APART-LUNG study will be performed in Germany (Hannover, Kiel, and Lübeck) and Denmark (Vejle), and an overview of assessments and examinations at each visit is given in Table 2. The following data are assessed at the time of baseline but refer to the time of radiation therapy: medical history, medication, demographics, body height and weight, Karnofsky performance score, histology, and tumor stage.

### 3.2. Examinations Related to Primary and Secondary Aims

Number of daily steps: Physical activity is documented using total daily step counts recorded by a smartphone-based application under real-life conditions, obtained for the first and fifth weeks of the patient’s radiation therapy course from the memory of the patient’s smartphone. Suitable patients treated with conventionally fractionated radiation therapy between 2023 and 2025 who own a smartphone that was used during treatment, had a step-counting application active during radiation therapy with stored historical data, and are willing and able to return to the institution are asked to visit the institution where they received their radiation therapy for lung cancer. Patients will be initially contacted by phone to check whether they have a smartphone and a step counter with a memory function and whether they are interested in potentially participating in this study. Patients will provide written informed consent when they visit the institution where they were irradiated. If the patient states that they do not require an additional reflection period, an assessment of the steps taken during the first and fifth weeks of the radiation therapy course from the memory of the patient’s smartphone will be performed by an investigator trained for the APART-LUNG study. The type of smartphone will be documented. After manual extraction of the step count for every single day from the patient’s smartphone, the data will be documented in the case report form. Subsequently, the daily steps will be added together and divided by the number of days to obtain the average number of steps.

#### Time per Day the Smartphone Was Worn Close to the Body

Patients will be asked to rate the time (average hours per day) that their smartphone was worn close to their body during the first and fifth weeks of their radiation therapy course.

### 3.3. Statistical Considerations

#### 3.3.1. Primary Aim

Our primary objective is to describe the pattern of physical activity during a course of radiation therapy, measured using total daily step counts recorded by a smartphone-based application. In addition to step counts, patients’ estimates of their mean daily wear hours in week 1 and week 5 are documented. If applicable, the wear hours may be determined from the health app on the patient’s smartphone. Week 1 is defined as days 1 to 7 following the initiation of radiation therapy, and week 5 is defined as days 29 to 35. For each patient, daily normalized step counts are calculated as described in Section 2.1. After discussion with an experienced statistician and several clinicians, a valid day is defined as a day with a minimum of eight hours of wear time, and a valid week means at least three valid days within the specified week. This threshold is not evidence-based but is rather chosen to ensure that the daily step counts reasonably reflect overall daily activity. Since no data have been found in the literature regarding this topic, the definition of a valid day may be adjusted during the course of the study to reflect a realistic scenario.

The primary endpoint is the within-patient difference in the normalized average step count per week (week 5 minus week 1). No imputation of invalid normalized average step counts per week is planned for the primary analysis, and the extent and pattern of missing data will be recorded descriptively. Given the exploratory nature of the study and the small sample size, advanced imputation methods are not planned. In addition to hypothesis testing, point estimates (e.g., mean or median change) and interval estimates (e.g., 95% confidence intervals) will be reported to quantify the magnitude and uncertainty of the observed within-patient change.

The primary estimand targets the average within-patient change in physical activity between radiotherapy weeks 1 and 5, and the population of interest comprises adult patients undergoing radiation therapy who use a smartphone-based step-counting application. Relevant intercurrent events such as incomplete smartphone carrying, temporary technical failures, changes in radiation therapy, and hospitalization may lead to missing step count data. These intercurrent events are addressed using a treatment policy strategy whereby all available valid data are included in the analysis, and days without sufficient carrying time are excluded without further adjustment. This estimand reflects the change in physical activity during radiation therapy as observed under real-world conditions of smartphone usage.

To describe the individual trajectories of the normalized average step count per week between week 1 and week 5, spaghetti plots will be created. In addition, summary statistics stratified by week will be provided for subjects with non-missing data, including the mean, standard deviation, median, first and third quartiles, minimum, and maximum. The normalized average step counts per week will be summarized using the same statistics. This analysis allows us to explore whether the normalized average step counts per week changed between week 1 and week 5. Given the modest sample size and the exploratory nature of the study, the Wilcoxon signed-rank test will be used as the primary inferential method, while a paired *t*-test may be reported as a supportive analysis if the distribution of within-patient differences is approximately normal. If diagnostic checks indicate material skewness or heteroskedasticity, a supportive analysis on the log scale will be presented as a ratio of geometric means with a 95% confidence interval, without changing the primacy of the original scale analysis.

The magnitude of the activity change will be quantified by estimating the mean within-patient difference together with the 95% confidence interval, interpreted descriptively. Standardized effect sizes for paired data (Cohen’s d) will also be reported to support interpretation and future planning.

A linear mixed-effects model with a fixed effect for time (week 1, week 5) and a random intercept for the patient to account for repeated measures will also be applied for exploratory analysis of the primary endpoint. The primary contrast estimates the adjusted mean difference between week 5 and week 1. The model reports the point estimate, a two-sided 95% confidence interval, and a descriptive *p* value. The primary analysis is on the original scale; in the case of skewness, a supportive analysis is performed on the log-transformed data, and the result is expressed as a ratio of geometric means with a 95% confidence interval. Exploratory subgroup analyses will assess whether the week 5 versus week 1 change differs across categories of relevant subgroups (for example, age category, performance status, and tumor type). The mixed-effects models are exploratory only, intended to identify potential trends for future adequately powered studies, and the present study is not intended to draw confirmatory statistical conclusions but to generate insights that may guide the design of subsequent, more robust clinical investigations. The combined approach, supplementing robust paired testing for the primary endpoint with exploratory trajectory modeling, maximizes insights from a limited sample while maintaining methodological appropriateness for a pilot study.

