### 3.5. Data Protection and Data Management

Details of data protection and data management have been previously reported for other prospective trials from the Interreg project HeAT [26,27,28]. The same applies to the distribution of the results. Collection of the data will occur according to the regulations of the Data Protection Act, and patient-related data will be recorded pseudonymously, handled in accordance with general data protection regulations, and analyzed by a professional external statistician following a previously defined statistical analysis plan. Study-related documents will be stored for 10 years. Scientific publications related to the study are reviewed by the external statistician. Moreover, the acronym APART-LUNG will be used in the corresponding publications.

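### The valid-day threshold may be changed during the study with no deadline, criterion or masking, so the rule that selects pairs for the primary analysis could follow the step counts already seen

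*Protocol article*

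**What the plan says.** Section 3.3.1 of the protocol article builds the primary analysis on two linked rules. The first is that "a valid day is defined as a day with a minimum of eight hours of wear time". The second requires three or more such days before a week counts as valid. On the eight-hour figure it is candid: "This threshold is not evidence-based but is rather chosen to ensure that the daily step counts reasonably reflect overall daily activity". Because no literature was found, it continues, "the definition of a valid day may be adjusted during the course of the study to reflect a realistic scenario".

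The consequences of failing the rule are stated in the same section. For weeks: "No imputation of invalid normalized average step counts per week is planned for the primary analysis". For days, under the estimand: "days without sufficient carrying time are excluded without further adjustment".

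Section 3.2 has a trained investigator read every daily count for both weeks from the phone by hand and enter it in the case report form. The subsection on wear time asks the patient for one recalled average of hours per day for each week; section 3.3.1 adds that a health app may be used where applicable. Section 3.5 says that the data will be "analyzed by a professional external statistician following a previously defined statistical analysis plan". That analysis plan is not among the documents available here.

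**The concern.** The eight-hour rule is an inclusion rule for the primary endpoint. A patient contributes a week 5 minus week 1 difference only if both weeks are valid, so moving the threshold changes who is analysed. The permission to move it carries four gaps: no date after which it lapses, no numerical trigger, no named decision-maker, and no condition that the decision be made without sight of step counts. What counts as realistic is left to judgement.

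The data are historical, so a patient's complete outcome is available at one visit, in a single-arm study with no masking described. Section 2.1 also states a directional expectation (a fall in steps is thought more likely), and section 2.2 a target of about 20 patients in the full analysis set. Either could colour a judgement of what is realistic without anyone intending it.

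Three outputs are exposed: the estimated change with its interval and descriptive p value; the feasibility result in section 2.1 (the proportion of patients with both weeks evaluable), which can only stay the same or rise when the threshold is lowered; and the later use of this cohort as the control group for the phase 2 trial.

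**Working it through.** **1. The plan's own figure.** Section 2.4 gives a detectable standardized difference of about 0.6 to 0.65 for n = 20, two-sided 5%, 80% power. The normal approximation is d = (z₀.₉₇₅ + z₀.₈₀)/√n = (1.960 + 0.842)/√20 = 0.626, which lies inside the stated range. The exact noncentral t gives 0.660, and 0.678 with the Wilcoxon efficiency factor 3/π. Fixing the valid-day rule changes none of this. The number of evaluable pairs does matter, and the threshold governs it:

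| Evaluable pairs | Detectable d (exact t, 80% power) |
|---|---|
| 20 | 0.66 |
| 18 | 0.70 |
| 16 | 0.75 |
| 14 | 0.81 |
| 12 | 0.89 |
| 10 | 1.00 |

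**2. How the threshold acts.** Where wear time is one recalled average per week, all seven days of that week carry the same hours and pass or fail together. The three-valid-day rule then never separates partial weeks. For illustration, take a patient who recalls 7 h in week 1 and 9 h in week 5. At 8 h, week 1 has 0 valid days, is not imputed, and the pair is lost. At 7 h or below, both weeks have 7 valid days and the pair enters. A change therefore adds or drops whole patients from about 20 and leaves retained patients' values untouched. Only where an app supplies daily wear hours would it also change which days are averaged.

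**3. Size if the choice follows the outcome.** The documents give no wear-time distribution, so the inputs below are assumptions. The simulation has no true change and differences independent of wear time, and applies the Wilcoxon signed-rank test at two-sided 5%.

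- Set A: 20 patients, mean wear 9 h, SD 2 or 3 h, correlation between weeks 0.8, 8,000 runs.
- Set B: 25 patients, mean wear 9 h, between-patient SD 2.5 h, within-patient SD 1 h, 6,000 runs.

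| Rule | Set A | Set B |
|---|---|---|
| 8 h fixed | 4.3–4.8% | 4.8% |
| Smallest p of 6, 8 h | 6.8–7.4% | not run |
| Smallest p of 6, 8, 10 h | 8.0–8.2% | 9.3% |
| Smallest p of 6, 7, 8, 9, 10 h | 9.6–10.1% | 11.1% |

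Monte Carlo error near 5% with 8,000 runs is √(0.05 × 0.95/8000) ≈ 0.24 percentage points. Over assumed mean wear of 8 to 10 h and between-patient SD of 2 to 3 h, the range for three to five thresholds is about 8–11%. In set A an average of 12.0 (SD 2 h) or 10.7 (SD 3 h) of the 20 pairs remained evaluable at 8 h, so pressure to revise the threshold is plausible.

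**4. Size if the choice follows wear time only.** With set B inputs, lowering the cut-off to 6 h whenever fewer than 70% of pairs are evaluable rejects in 5.2% of null runs (4.4–5.6% across four other input sets). Selection on wear time leaves the differences centred on zero when the two are independent.

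**5. Effect on the planning quantities.** Under smallest-p selection in the same null setting, the mean change stays near zero, the average SD of the differences falls from 0.98 to 0.95 (0.03/0.98 ≈ 3%), and coverage of the 95% interval falls to about 90%.

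**The case against.** **The study is exploratory.** Section 2.4 says that formal testing power is not targeted and that inference is descriptive, and section 3.3.1 disclaims confirmatory conclusions. This stands, and it limits severity: the inflated rejection rates break no error rate that the study claims to control. It does not remove the point, because the estimates are meant to inform the phase 2 sample size and the cohort is to be reused as a control group.

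**Adjustment is reasonable where no literature exists.** This also stands. The wording reads naturally as a concern for realistic wear time, and step 4 shows that such a change does no harm to the error rate. The weakness is that the text does not confine the change to that basis.

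**The planning SD hardly moves.** True under the assumed inputs, even with deliberate selection (about 3%). The effect falls mainly on the p value, the interval coverage and the feasibility proportion.

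**Stronger readings that the article does not support.** A reader might infer that section 3.3.1 contradicts the analysis plan mentioned in section 3.5. It does not: a threshold settled during recruitment and fixed before the external statistician's analysis satisfies both, and the unseen plan may contain that freeze. A reader might also infer that the people deciding will have seen every patient's outcome. The article shows only that investigators extract counts locally in Germany and Denmark. It describes no interim pooling and does not say who decides, so access is possible but not established. Nor does anything suggest that choosing on the outcome is intended.

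**Conclusion.** The point holds as a SHOULD-FIX. It rests on an affirmative permission in the current text, not on a detail left to the analysis plan. The rule it leaves open selects the pairs for the primary analysis while step counts are already being extracted unmasked. The fault lies in the missing deadline, criterion and masking, and not in adjustment as such.

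The worst case is null rejection of about 8–11% instead of about 5%. That assumes deliberate choice among three to five thresholds, the wear-time inputs listed above, and differences independent of wear time. The last is a simplification, because wear hours are also the endpoint's denominator. These figures illustrate what the wording allows and do not predict what will happen. Treating the point as a mandatory correction would go too far for a pilot whose inference is descriptive.

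**What to change.** Either of two changes to section 3.3.1 is enough.

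- **Freeze.** State that the eight-hour threshold is fixed before the first step count is extracted, and pre-specify 6 h and 10 h as sensitivity analyses.
- **Controlled change.** Allow one dated change before analysis, based only on the wear-time distribution and made by someone who has not seen step counts.

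In both cases, report the primary result and the proportion of evaluable patients at 8 h. A line in section 3.5 saying that the analysis plan records the final threshold and its date would make the safeguard visible.

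The cost is a sentence or two and two reruns of the primary analysis. The downside is some lost flexibility if many weeks fall below 8 h; the 6 h sensitivity analysis or the controlled change covers most of that. The step should be taken before extraction starts, because masking cannot be restored afterwards.

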
## Figures and Tables

**Table 1 clinpract-16-00080-t001:** Inclusion and exclusion criteria for the APART-LUNG study.

Inclusion criteria	1. Histologically proven lung cancer 2. Treatment with ≥50 Gy of conventionally fractionated radiation therapy 3. Possession of and ability to use a smartphone plus a step counter 4. Age ≥18 years 5. Written informed consent 6. Capacity of the patient to consent
Exclusion criteria	1. Expected non-compliance 2. Cognitive impairment 3. Inability to provide informed consent independently 4. Life expectancy less than the study period

**Table 2 clinpract-16-00080-t002:** Overview of enrollment, assessments, and examinations.

	Screening	Baseline	Week 1 of Previous Radiation Therapy	Week 5 of Previous Radiation Therapy
Demographics including age	X			
Parameters of radiation therapy	X			
Medical history and concomitant diseases		X		
Concomitant medication		X	X	
Performance status		X		
Histology of lung cancer		X		
Study-related procedures				
Informed consent	X			
Inclusion criteria	X			
Exclusion criteria	X			
Time the smartphone was worn close to the body at the time of radiation therapy			X	X
Number of steps per day			X	X

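### The primary analysis is labelled treatment policy but is an available-day, complete-pair estimate, so the week 5 minus week 1 change may be biased, plausibly towards zero

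*Protocol article*

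**What the plan says.** The relevant text is in Section 3.3.1 (Primary Aim) of the Protocol article.

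- **Events:** "Relevant intercurrent events such as incomplete smartphone carrying, temporary technical failures, changes in radiation therapy, and hospitalization may lead to missing step count data".
- **Strategy:** "These intercurrent events are addressed using a treatment policy strategy whereby all available valid data are included in the analysis".
- **Low-carry days:** the same sentence gives the rule in full: "all available valid data are included in the analysis, and days without sufficient carrying time are excluded without further adjustment".
- **Validity rule:** "a valid day is defined as a day with a minimum of eight hours of wear time". A week needs at least three such days.
- **Invalid weeks:** "No imputation of invalid normalized average step counts per week is planned for the primary analysis". Missing data are to be described only.

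The primary test is the Wilcoxon signed-rank test on the paired difference in steps per wear hour. Section 3.2 obtains wear time by asking the patient for one average figure per week. Section 3.3.1 allows health-app hours instead where they are available. Section 2.1 plans to report the share of patients with both weeks evaluable and the operational reasons when they are not. It also states that the study will be used to size the phase 2 trial and that the cohort will be its control group.

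**The concern.** A treatment policy strategy uses the outcome as observed, whatever the intercurrent event. Here the occurrence of one listed event, incomplete carrying, is itself the reason for removing data. Weeks lost to another listed event, hospitalization, are simply absent. What remains is an available-day, complete-pair analysis. It estimates the stated target, the average within-patient change, only if loss of days and pairs is unrelated to that change.

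The protocol gives grounds to doubt this. It names hospitalization as a cause of missing step counts, it expects activity to fall, and the Introduction notes that "Patients who experience significant fatigue may be unable to complete their entire radiation therapy course as initially planned". If patients who become ill by week 5 are the ones without a valid week 5, the observed decline is too small. The main question is whether activity holds steady or falls. The answer feeds the phase 2 sample size and supplies that trial's control group, so the exploratory status of the study does not make the error harmless.

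**Working it through.** **1. The plan's own figure.** Section 2.4 gives a detectable standardized paired difference of about 0.6 to 0.65 for n = 20, two-sided 5%, 80% power. The normal approximation gives (1.960 + 0.842)/√20 = 0.626, inside that range. The exact noncentral t gives 0.660, with 78.7% power at 0.65. The figure is reproduced well enough, and 0.65 serves below as the assumed size of a true decline.

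**2. What the 8-hour rule does with one recalled weekly average.** Assumed values: a usual day has 4,000 steps over 10 h (400/h); a day in bed has 500 steps over 4 h; week 1 has no bed days; recall is accurate.

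- One bed day: wear (6×10 + 4)/7 = 9.14 h, week kept. Rate (6×4,000 + 500)/64 = 383/h, a change of -4.3%.
- Two bed days: wear (5×10 + 2×4)/7 = 8.29 h, week kept. Rate (5×4,000 + 2×500)/58 = 362/h, a change of -9.5%.
- Three bed days: wear (4×10 + 3×4)/7 = 7.43 h, below 8 h. All seven days fail and the pair is lost, although the rate would be (4×4,000 + 3×500)/52 = 337/h, a change of -15.9%.

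With a weekly average, single days cannot be picked out. The whole week passes or fails, so selection acts on patients. In this example the patient with the largest fall is the one who leaves.

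**3. Size of patient-level selection.** The documents give no loss rate and no link between loss and change, so both are assumed. True standardized change is -0.65; 10% to 30% of pairs are lost; the log-odds of loss vary by 0.7 to 1.5 per standard deviation of the change, in either direction. Simulated mean change among retained pairs:

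| Pairs lost | Larger declines lost more often | Loss unrelated | Smaller declines lost more often |
|---|---|---|---|
| 10% | -0.58 to -0.52 | -0.65 | -0.72 to -0.77 |
| 20% | -0.52 to -0.42 | -0.65 | -0.78 to -0.87 |
| 30% | -0.46 to -0.33 | -0.65 | -0.84 to -0.98 |

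In the first column the decline shrinks by between 1 - 0.58/0.65 = 11% and 1 - 0.33/0.65 = 49%.

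**4. Day-level selection, possible only where the health app gives daily wear.** Simulation with the 8-hour/3-day rule, assuming about 92% of days valid in week 1 and 76% in week 5. Change in steps per wear hour, all days versus valid days:

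- Sick days have low wear and a low step rate: -57.4 versus -47.4. The decline shrinks by 10.0/57.4 = 17%.
- Wear unrelated to step rate within the week: -57.0 versus -57.1. No bias.
- Phone carried mainly while walking, so short-wear days have high hourly rates: -27.2 versus -31.5. The decline grows by 4.3/27.2 = 16%.
- The same carrying pattern with a smaller fall in steps: +20.2 versus +0.7. Exclusion removes most of a rise that comes only from shorter wear.

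**5. Why the form of an all-days analysis matters.** Take two bed days with 500 steps over 1 h each. Averaging daily rates gives (5×400 + 2×500)/7 = 429/h, an apparent rise of 7%. Total steps over total wear gives 21,000/52 = 404/h (+1%). Unnormalized steps average 21,000/7 = 3,000 per day against 4,000, a fall of 25%.

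**The case against.** Five objections deserve an answer.

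- **Hospital days are not excluded as such.** A hospitalized patient with eight hours of wear is counted, and exclusion is by measurement validity. This is correct. But incomplete carrying is itself on the list of events, and hospital days below the threshold are lost. The contradiction remains in the printed sentence.
- **The direction of bias is not established.** A reader might infer that every exclusion removes the sickest days or patients and so must pull the change towards zero. The documents do not support that. They give no link between wear and illness, and with a per-wear-hour endpoint, step 4 of the working shows shrinkage, no effect or exaggeration. A reader might also suppose that two bed days would simply vanish and leave no change at all. Under the default weekly average they are kept and the fall is still visible.
- **Sensitivity analyses may be in the analysis plan.** Section 3.5 refers to one, and it is not shown. Their absence from the article is therefore not the finding; the conflict in the estimand text is.
- **The loss is partly handled.** Missingness will be described, and the exploratory random-intercept model can keep patients with one valid week. That model assumes missing at random and is not the primary analysis.
- **The Limitations section is candid.** It covers recall error and selection by phone ownership and survival, but not selection through dropped days or pairs.

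A reader might also take the Table 1 criterion, "Treatment with ≥50 Gy of conventionally fractionated radiation therapy", to screen out patients who stopped early. The wording does not say whether the prescribed or the received dose is meant, and altering it would change the target population. No change to it is proposed.

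**Conclusion.** The point holds as a conflict between the estimand and the analysis. The strategy claimed is treatment policy; the analysis described uses available days and complete pairs, and is valid only if missingness is unrelated to the change in activity. The week 5 minus week 1 change may therefore be biased. Bias towards zero is the plausible direction, because the protocol names hospitalization as a cause of missing data, but it is not certain.

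No single size can be given. Under the assumptions in the working, a true standardized change of -0.65 could be reported as anything from -0.33 to -0.98, depending on how many pairs are lost and which ones. Where wear is one recalled weekly average, the mechanism is mainly the loss of whole patients. The text should be corrected before the data are analysed, since the estimates and the cohort pass directly into phase 2.

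**What to change.** 1. **Reword the estimand in Section 3.3.1.** Call incomplete carrying and technical failure missing data. Keep treatment policy for hospitalization and changes in radiation therapy, and use all recorded steps on those days. State how this applies to a week whose only wear figure is a weekly average below eight hours.
2. **Add a sensitivity analysis without the 8-hour/3-day rule,** using every day with recorded steps. Report it as total weekly steps over total weekly wear hours and as unnormalized steps. Do not average daily rates, which very short wear can inflate. Section 3.2 already has steps extracted for each day.
3. **Add a signed-rank sensitivity analysis with worst ranks.** Pairs with a valid week 1 and a week 5 lost to illness or hospitalization receive a difference below any observed one, tied among themselves. Record illness and hospitalization as explicit codes among the reasons for non-evaluable pairs that Section 2.1 plans to report; Table 2 lists no such item at present.

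The cost is a revised paragraph, two further analyses and an added reason code. The sensitivity results will be noisier because they include low-wear days.
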